### Recruitment {15}

We will benefit from a significant network of psychiatrists, psychologists, and addictology and health professional workers from the University Hospital of Martinique (UHM) and the Saint-Esprit Hospital (SEH; Martinique) to steer any patient volunteering to participate in the study. To date, both UHM and SEH inpatient residential addictology clinic provide access to 30 beds for TAU for CUD, reaching up to 200 patients per year.

## Assignment of interventions: allocation

### Sequence generation {16a}

The Research Electronic Data Capture (REDCap) secure web application will be used for randomizing participant allocation to the experimental or active control therapeutic arm. The randomization will be stratified per investigation center (UHM or SEH), with an allocation ratio of 1:1 to the therapeutic arms and following a randomly permuted per-block order.

### Concealment mechanism {16b}

The research psychiatrist or psychologist will be informed of the participant allocation only at the start of the intervention phase, following a sealed opaque envelope-based procedure.

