#### Randomization

Eligible patients will be randomized by the research psychiatrist or psychologist in charge of the inclusion visit, using the Research Electronic Data Capture (REDCap) secure web application, in the VRCET + (experimental) or PCET (active control) therapeutic arm.

After randomization, participants will be invited to complete baseline self-reported measures as well as to perform a craving induction task related to primary and secondary research objectives. This craving induction task will consist of three 7-min 30 exposures and will systematically start with one VRE to neutral cues, followed by one VRE and one PCE to a cocaine-related situation. The order of these two exposures to cocaine cues (i.e., VRE thus PCE or PCE thus VRE) will be randomly counterbalanced for controlling for potential cue-induced carry-over effect between one exposure to the other. The exposures’ order sequence generation for each participant will be generated by the research methodologist, using the Research Randomizer secure web application, and provided to the investigator within sealed opaque envelope for the inclusion visit.

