#### Experimental or active control therapy (3 weeks)

Participants included will start therapy (experimental or active control arm) within 1 week after the inclusion visit as follows:VRCET + (experimental arm): 2-week phase of 10 VRCET sessions, followed by a 1-week phase of 5 MFCT sessions. The VRCET phase will essentially consist of 40 VRE to a progressive hierarchy of 5 diversified cocaine-related situations. The MFCT phase will be in accordance to the “Memory Focused Cognitive Therapy for Cocaine Use Disorder” therapist guide (for request: [39]), and will consist of cognitive restructuring and memory reconsolidation procedures along with imagery exposure to arousing memories of cocaine use.PCET (active control arm): 3-week phase of 15 PCET sessions. The PCET phase will essentially consist of 60 VRE to a progressive hierarchy of 5 diversified cocaine-related situations.

Both VRCET + and PCET sessions will last 1 h 30 min and will be delivered in an intensive 1:1 intervention format, on a daily basis, from Monday to Friday. The facilitator of VRCET + and PCET may differ, but each patient will have only one facilitator.

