### Implementation {16c}

The allocation sequence will be generated by the research data manager from the UHM methodology unit before starting the research and following a confidential handbook document. Each research psychiatrist and psychologist will oversee the assignment of participants to interventions in their respective investigation center.

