## Assignment of interventions: blinding

### Who will be blinded {17a}

Patients and researchers will not be blinded after assignment to interventions given significant delivery modalities between VR-based and picture-based exposure therapies. Only the data manager in charge of the allocation sequence will be blinded to the assignment.

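### The plan gives two points at which the arm is disclosed (REDCap at the inclusion visit, sealed envelope at therapy start), so it does not fix whether baseline craving is measured with the arm known

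*Protocol article*

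**What the plan says.** All places are in the protocol article.

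- **Randomization** (Participant timeline {13}): "Eligible patients will be randomized by the research psychiatrist or psychologist in charge of the inclusion visit", using REDCap. The next paragraph continues: "After randomization, participants will be invited to complete baseline self-reported measures", together with the craving induction task. The schedule (Table 4) likewise puts allocation at T0, week 0.
- **Sequence generation {16a}**: the REDCap "secure web application will be used for randomizing participant allocation to the experimental or active control therapeutic arm", stratified by centre, 1:1, "following a randomly permuted per-block order".
- **Concealment mechanism {16b}**: the research psychiatrist or psychologist is "informed of the participant allocation only at the start of the intervention phase, following a sealed opaque envelope-based procedure".
- **Implementation {16c}**: the methodology unit's data manager generates the sequence in advance. "Each research psychiatrist and psychologist will oversee the assignment of participants to interventions in their respective investigation center".
- **Experimental or active control therapy (3 weeks)**: "Participants included will start therapy (experimental or active control arm) within 1 week after the inclusion visit".
- **Who will be blinded {17a}**: "Patients and researchers will not be blinded after assignment to interventions".
- **Statistical methods {20a}**: the primary analysis is a t-test on the change in score from T0 to T2.

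**The concern.** The role that carries out the REDCap randomisation at V0 is also the role said to learn the arm later, from an envelope. The article does not say that REDCap withholds its result from the person who runs it. It does not say that the envelope is how a REDCap result is passed on, or which of the two governs.

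The order of events matters because the trial is open and the primary outcome, craving on the CEQ, is self-reported. A baseline taken before anyone knows the arm cannot be affected by it. A baseline taken afterwards can: a patient who knows which therapy is coming, or an assessor who knows it, may report or elicit craving differently. That T0 value is one of the two terms in the primary change score.

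**Working it through.** No stated figure is at issue, so the check is a comparison of the text, followed by the algebra of the change score.

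**1. Who acts, and when the arm is known**

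- *Account A* (Randomization, Sequence generation, Table 4): the inclusion-visit clinician randomises in REDCap at V0. If the result is displayed, the arm is known at V0.
- *Account B* (Concealment mechanism): the same role is told by envelope when the intervention phase starts.
- The gap between the two is anything up to 1 week, from the rule on starting therapy.

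**2. Where the baseline falls**

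- Under both accounts the baseline CEQ comes after randomisation.
- Under A, with the result displayed, it is collected with the arm known.
- Under B, it is collected at V0, before the clinician knows the arm.
- Who will be blinded {17a} lifts blinding for patients and researchers from assignment onward. Read with Randomization, that points to A. Read with Concealment mechanism, it could mean from the start of therapy.

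**3. Does other text settle it?** No.

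- The Randomization section also uses sealed opaque envelopes, but for the order of the VR and picture exposures, a different randomisation. The concealment section may have merged the two. The article does not say.
- The data manager generates the sequence {16c} but is described as blinded to the assignment {17a}, so it is unclear who would prepare arm envelopes.
- Confidentiality {27} builds the arm into each participant's identification code. If the code is created at V0, the arm is visible then. The article does not say when it is created.

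**4. What an informed baseline would do**

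For each patient let the decrease be D = CEQ(T0) − CEQ(T2). The estimated effect is mean D in VRCET+ minus mean D in PCET. Suppose knowing the arm shifts mean baseline craving by a in VRCET+ and by b in PCET, with T2 unchanged. Then

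shift in estimated effect = a − b.

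The shift is one for one. To convert the unit: Outcomes {12} gives the CEQ-S total as 11 to 110, which is 11 items scored 1 to 10. Each single point per item in a − b would be 11 × 1 = 11 points on the total. This is a conversion, not an estimate. The document gives no standard deviation and no basis for the size or sign of a − b.

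**The case against.** The strongest reply is that the two accounts can be made to agree. Randomization says who triggers the allocation, not that the result appears on that person's screen. A REDCap allocation disclosed later by envelope fits both sections, and the confidential handbook mentioned under Implementation {16c} may describe it. This stands as a possibility, and it is why the point is an unresolved procedure and not a proven error. It does not remove the point, because the article fills in the sequence, concealment and implementation items and what it writes there does not connect.

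A reader might infer more: that allocation is unconcealed and enrolment open to selection. The documents do not support that.

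- Concealment requires the next arm to be unknown until consent and eligibility are settled. Account A randomises patients already found eligible, and account B discloses later still. Either one, properly run, conceals.
- No section says that envelopes for future patients are kept at the sites, and sealed opaque envelopes are a recognised method.

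A reader might also point to permuted blocks within centre in an open trial. If blocks were fixed and their size known to staff, the share of assignments that could be predicted with certainty would be:

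- size 2: 1/2 = 50%
- size 4: 8/24 = 33% (of the six orders, two leave the last two places certain and four leave the last one)
- size 6: 30/120 = 25%

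But the block size is not given, nothing says it is fixed or known, and a journal article may leave it to the full protocol. The risk is also the same under REDCap or envelopes, so it does not bear on the conflict between them. A false-positive rate would need further assumptions: that staff act on every certain slot, and how far the outcomes of the patients they steer to each arm differ. I therefore give none.

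**Conclusion.** The concern holds in a limited form. As written, the article does not fix who sees the arm and when, because it gives the same role two disclosure points up to a week apart and does not link them. No breach of concealment is shown.

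The consequence the text does support is at baseline: whether the T0 CEQ is taken with the arm known depends on which section governs. If it is, any resulting difference between arms at baseline enters the primary estimate in full, by an amount that cannot be estimated from the document. This rests on two readings: that the baseline measures follow randomisation, which is stated, and that a clinician who randomises in REDCap may see the result, which is usual but not stated. It should be corrected because the remedy is cheap and the ambiguity touches the primary endpoint.

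**What to change.** State one mechanism, in the same terms, under Randomization, Concealment mechanism {16b} and Implementation {16c}:

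- Allocate the arm only through REDCap, from a list loaded by the methodology unit that the sites cannot see.
- Drop the envelope step for the arm. Keep envelopes for the order of the VR and picture exposures.
- Release the arm only after consent, eligibility and every V0 baseline measure (CEQ-F, CEQ-S and the whole craving induction task included) are entered and locked.
- Make the blinding statement {17a} and the participant code {27} consistent with this, so that no code showing the arm exists before release.
- For patients already enrolled (recruitment began in May 2023), report which mechanism was used and whether baseline came before the arm was disclosed. The audit trail under Data management {19} records dates of data entry. Because most questionnaires are on paper, entry may have followed completion, and the source forms may be needed.

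If the blocks turn out to be of fixed size, varying sizes not disclosed to the sites are an optional extra.

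The cost is a wording change and a small reordering of V0, with the paper forms entered before the arm is released. The interval of up to a week before therapy leaves room for this. No extra visit is needed.

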### Implementation {16c}

The allocation sequence will be generated by the research data manager from the UHM methodology unit before starting the research and following a confidential handbook document. Each research psychiatrist and psychologist will oversee the assignment of participants to interventions in their respective investigation center.

## Assignment of interventions: blinding

### Who will be blinded {17a}

Patients and researchers will not be blinded after assignment to interventions given significant delivery modalities between VR-based and picture-based exposure therapies. Only the data manager in charge of the allocation sequence will be blinded to the assignment.

### Procedure for unblinding if needed {17b}

No unblinding procedure will occur given our trial design open-label nature.

## Data collection and management

### Plans for assessment and collection of outcomes {18a}

Study outcomes will be mostly assessed and collected using paper-based self-report questionnaires. Reliability or medical certification of these psychometrically validated self-report and physiological instruments are detailed in the “Outcomes {12}”. The study assessors will be trained for assessing and collecting outcomes prior to the research. Patient individual data will be recorded on an online hospital server using the Research Electronic Data Capture (REDCap) secure web application.

### Plans to promote participant retention and complete follow-up {18b}

Prior to each measurement time (T0, T1, T2, and T3), participants will be reminded of the therapeutic and scientific importance of dully completing each intervention and assessment phase. For the follow-up assessment, the investigators will contact the participants to collect study outcomes. A 20 € voucher will be offered to any outpatient participant in the follow-up assessment phase willing to use public transport for coming to their respective investigation center. Participants will be reminded that they may discontinue their consent to participate at any time during protocol, without justifying any reason and with no impact on their TAU. Data collected in participants who withdraw their consent will be analyzed.

### Data management {19}

For each patient included on the trial, an e-CRF will be generated and dully completed with participants’ individual data collected along the protocol. Access to this e-CRF will be granted through the Research Electronic Data Capture (REDCap) secure web application, with rights (e.g., data visualization and modification), identification, and password sequences specific to each study member. Data entry will be secured using a crypted 128 bits SSL mode directly on internet navigator and recorded (data provider, data provided, and date of data entry) following an audit trail system.

### Confidentiality {27}

Any study professional member (e.g., research psychiatrist, psychologist, or data manager) having access to participants’ individual data will be bound to professional secrecy, which is in accordance with the French public health code. The use of participants’ individual data collected will be systematically anonymized following a codification participant identification procedure. To do so, each code generated for each participant will include the center in which the investigation is conducted (UHM or SEH), the intervention assignment (experimental or active control arm), and the inclusion number (e.g., 001), following a chronologic sequence. Each principal investigator will oversee the confidentiality of the data using a sealed paper-based record in which participant authentication data (first name, family name, and date of birth) will be related to their identification code.

### Plans for collection, laboratory evaluation and storage of biological specimens for genetic or molecular analysis in this trial/future use {33}

N/A: no collection, laboratory evaluation, and storage of any biological specimens for genetic or molecular analysis in this trial/future use.

## Statistical methods

### Statistical methods for primary and secondary outcomes {20a}

Statistical analyses for principal and secondary outcome will be computed from self-report scales raw total scores or physiological signals (i.e., blood pressure, skin temperature and conductance) using, respectively, R Statistical [66] and OpenSignals (© PLUX S.A.) software. Our comprehensive data working R code, including R packages and inferential statistical hypothesis testing assumptions (Gaussian distribution, homoscedasticity, etc.), will be made available. For each primary or secondary variable of interest, descriptive statistics (n, min, max, median, q1, q3, iqr, mean, sd, se, and mean ci) will be computed using the *rstatix R* package. Primary inferential statistical analyses will consist of two-tailored independent *t*-tests on score changes between T0 (baseline) and T2 (post-treatment) in the experimental (i.e., VRCET +), compared with the active control therapeutic arm (PCET). In case of mostly non-normal variable distributions but symmetrical score differences around the median, Friedman and Bonferroni-corrected Wilcoxon signed-rank tests will be performed to test and contrast score differences between the conditions using *stats* and *rstatix R* packages [67]. In case of non-symmetrical paired score differences, Bonferroni-corrected Sign tests will be performed. Causal mediation analyses will be adjusted for confounding factors. Cohen’s d, Kendall’s W, and Cliff’s delta effect sizes for score changes across treatment arms (“negligible,” “small,” “medium,” and “large” effect for Cliff’s d inferior to 0.15, 0.33, 0.47, and superior to 0.47; [68]) with 95% CIs will be computed using *irr* and *effsize R* packages.

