### Outcomes {12}

Our primary outcome will consist in the decrease of the self-reported cocaine craving as assessed with the French Craving Experience Questionnaire (CEQ; [53, 54]. The CEQ is an 11-item retrospective measure of cocaine craving containing two subscales: craving strength (CEQ-S) and frequency (CEQ-F). Each item is completed by the participants on a 10-point scale, from “not at all” (1) to “extremely” (10). The CEQ has shown good psychometric properties [54]. Means of CEQ-S and CEQ-F total scores will be analyzed. Finally, the CEQ will be administered before treatment (V0), after 2 weeks of treatment (V1; VRCET vs. PCET), post-treatment (V2; VRCET + vs. PCET), and 1-month post-treatment (V3; VRCET + vs. CET). The CEQ-S will be administrated immediately after a 7-min VRE to a cocaine-related situation, with a similar scenario to the CET situation 5 (Table 1) but across different virtual environments, avatars, and item appearances (Fig. 9). The CEQ-F will be administrated retrospectively, targeting the last 14-day period. (Table 4)

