### Sample size {14}

We calculated a required sample size of 54 participants to randomize with G*Power [64], on the basis of two-tailed independent *t*-tests, to detect large effect from our experimental treatment (VRCET +) over our control therapeutic condition (PCET) in reducing cocaine craving [39, 65], given a 0.05 statistical significance threshold, a 0.95 statistical power, and accounting for potential dropouts in our hospitalized inpatients.

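### The planned unadjusted t-test on CEQ change is valid, but generally less precise than a baseline- and centre-adjusted model that uses data already collected

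*Protocol article*

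**What the plan says.** The Statistical methods section {20a} names the primary inferential analysis: two-sided independent t-tests on "score changes between T0 (baseline) and T2 (post-treatment) in the experimental" arm, compared with the PCET arm. It lists no covariate for this comparison. The only adjustment it mentions belongs to another analysis: "Causal mediation analyses will be adjusted for confounding factors".

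Both natural adjusters are already in the trial. Outcomes {12} says that "the CEQ will be administered before treatment (V0), after 2 weeks of treatment" and at later visits, and that "Means of CEQ-S and CEQ-F total scores will be analyzed". Sequence generation {16a} says: "The randomization will be stratified per investigation center (UHM or SEH), with an allocation ratio of 1:1 to the therapeutic arms".

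The Sample size section {14} rests on the same kind of test: "We calculated a required sample size of 54 participants to randomize with G*Power", using two-tailed independent t-tests, alpha 0.05, power 0.95, a large effect with no numerical value, and an allowance for dropout with no stated rate.

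**The concern.** The primary test is written out, so this is a choice the protocol makes and not a detail left to an analysis plan.

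A change score uses the baseline value but fixes its coefficient at 1. Unless the true regression slope of T2 on T0 is 1, the change stays correlated with baseline. This has two consequences:

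- Baseline variation that a fitted slope would remove stays in the error term.
- If the arms differ at baseline by chance, the arm that starts higher tends to show the larger fall through regression to the mean. That shifts the treatment contrast for the sample in hand.

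Separately, the stratification factor used in the randomisation is absent from the analysis. With 54 patients, precision that costs no recruitment is worth having.

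**Working it through.** **Inputs.** From the protocol: 54 randomised at 1:1, so 27 per arm; two-sided alpha 0.05; target power 0.95; t-test on change; two centres as strata. Not in the protocol, so assumed and varied: the effect size d (in SDs of change), the correlation rho between T0 and T2 CEQ, and the ratio of the T2 SD to the T0 SD.

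**The plan's own figure.** The 54 cannot be reproduced from stated inputs, because neither d nor the dropout rate is given. By the noncentral t distribution, 27 per arm gives power 0.950 at d = 1.0 with nobody lost. At d = 0.8 it gives 0.822, and 0.95 would need 42 per arm (84 in all) before dropout. Both values of d are carried forward.

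**Variance.** With a common SD s at T0 and T2:

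- Change score: 2(1 − rho)s²
- ANCOVA: (1 − rho²)s²
- Ratio: (1 − rho²) / [2(1 − rho)] = (1 + rho)/2

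**Power at 27 per arm.** The change-score test has 54 − 2 = 52 degrees of freedom. The model with arm, baseline and centre has 54 − 4 = 50. The effect is divided by the square root of the variance ratio. The last column is 54 divided by that ratio.

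| rho | Variance ratio | Power, d = 0.8 (change score 0.82) | Power, d = 1.0 (change score 0.95) | Patients a change-score test needs to match ANCOVA on 54 |
|---|---|---|---|---|
| 0.3 | 0.65 | 0.95 | 0.99 | 83 |
| 0.5 | 0.75 | 0.91 | 0.99 | 72 |
| 0.7 | 0.85 | 0.88 | 0.97 | 64 |
| 0.8 | 0.90 | 0.86 | 0.97 | 60 |
| 0.9 | 0.95 | 0.84 | 0.96 | 57 |

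A small-sample penalty for estimating the covariate slopes, 1 + 1/(2n − 4) on the variance, lowers these powers by less than 0.01 (for example 0.914 to 0.909 at rho 0.5, d = 0.8).

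**Unequal SDs.** If the T2 SD is k times the T0 SD, the ratio is (1 − rho²)k² / (1 + k² − 2·rho·k).

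- rho = 0.7, k = 1.2: 0.51 × 1.44 / (1 + 1.44 − 1.68) = 0.734 / 0.76 = 0.97, so almost no gain.
- rho = 0.7, k = 0.8: 0.51 × 0.64 / (1 + 0.64 − 1.12) = 0.326 / 0.52 = 0.63, a larger gain than with equal SDs.

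**Chance imbalance.** The difference in mean baseline CEQ between arms has an SD of √(2/27) = 0.27 baseline SDs. Given an imbalance D, the change-score contrast is shifted by (rho − 1)D when the SDs are equal. At rho = 0.5, a typical imbalance shifts it by 0.5 × 0.27 = 0.14 SD; at rho = 0.9, by 0.1 × 0.27 = 0.03 SD. ANCOVA removes this shift if the linear model holds.

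**Centre.** Suppose centre explains a share R² of the variance of change and the arms are balanced within centre. Adjustment then divides the effect by √(1 − R²), with 51 degrees of freedom. At d = 0.8, power goes from 0.822 to 0.826, 0.841 and 0.860 for R² of 1%, 5% and 10%. The true alpha of the unadjusted test is about 0.049, 0.045 and 0.039. The documents give no centre effect.

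**The case against.** The strongest reply is that nothing here is an error. Under 1:1 randomisation the change-score t-test is unbiased over repeated randomisations and controls type I error. It matches an outcome declared as a decrease in craving and the test used for sizing. That stands: this is a recommendation about efficiency, with bias arising only conditionally on the imbalance actually seen.

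Four stronger readings are tempting, and the documents do not support them:

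- **The analysis ignores baseline CEQ.** It does not. Change from T0 contains the baseline value, with its slope fixed at 1.
- **The trial is underpowered.** That follows only if the large effect means 0.8. The protocol states no d, and 54 patients give exactly 0.95 at d = 1.0 without dropout.
- **Omitting centre inflates the standard error whenever centres differ.** A constant difference between centres in CEQ level cancels in a change score. Only a difference in change matters, and its effect is probably small.
- **ANCOVA always brings a worthwhile gain.** The gain fades as rho approaches 1, and it nearly vanishes in the rho 0.7, k = 1.2 example.

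The timing of baseline is a separate matter. The Randomization section says "After randomization, participants will be invited to complete baseline self-reported measures", while the concealment section has the research psychiatrist or psychologist learn the allocation only when the intervention starts. Any weakness there affects the change score and the ANCOVA alike, so it does not favour either. Moving the baseline would be a procedural change in a trial that began recruiting in May 2023.

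**Conclusion.** The point holds as an avoidable loss of precision in a stated primary analysis. It does not make the planned test invalid.

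With equal SDs at T0 and T2, adjustment cuts the variance by 5% to 35% for rho from 0.9 to 0.3. The practical value depends on the effect size. It is appreciable if the true effect is near 0.8 SD of change, and modest near 1.0 SD, where the planned test already reaches 0.95 with complete data. Dropout makes it more useful: at an assumed 22 per arm, d = 1.0 and rho 0.5, power is 0.90 for the t-test and 0.96 adjusted.

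These figures rest on assumed values of d, rho and the SD ratio. The main reason for the centre term is agreement between analysis and design, with little precision to be expected from it.

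**What to change.** Make the primary analysis a linear model of T2 CEQ, for each subscale, on treatment arm, T0 CEQ and centre. Report the adjusted mean difference with its 95% confidence interval. Keep the independent t-test on T0–T2 change as a sensitivity analysis.

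The change should be specified before outcome data are compared by arm. It costs a revision of the analysis wording, a few lines of R and two degrees of freedom. It needs no further patients, visits or measurements.

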### Trial design {8}

This project is a two-center parallel, randomized, controlled, superiority trial, with a 1:1 allocation ration and two 3-week treatment arms (15 meetings): a VRCET-based experimental arm (VRCET + ; 2 week VRCET + 1 week MFCT) and a PCET-based active control arm.

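### The non-normal fallback for the primary arm comparison consists only of paired tests, which cannot compare two independent randomised arms

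*Protocol article*

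**What the plan says.** Trial design {8} describes a "two-center parallel, randomized, controlled, superiority trial" with 1:1 allocation, so each patient belongs to one arm only. No matching of patients across arms is described anywhere.

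Statistical methods {20a} makes the primary analysis a two-sided independent t-test on "score changes between T0 (baseline) and T2 (post-treatment) in the experimental (i.e., VRCET +), compared with the active control therapeutic arm (PCET"). The next sentence deals with distributions that are mostly non-normal but have symmetrical differences: "Friedman and Bonferroni-corrected Wilcoxon signed-rank tests will be performed to test and contrast score differences between the conditions". The sentence after that covers asymmetry: "In case of non-symmetrical paired score differences, Bonferroni-corrected Sign tests will be performed". The paragraph then lists Cohen's d, Kendall's W and Cliff's delta as "effect sizes for score changes across treatment arms". The article names no rank test for two independent groups.

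The article has one within-patient comparison of exposure types, the craving induction task at inclusion, which "will systematically start with one VRE to neutral cues, followed by one VRE and one PCE to a cocaine-related situation". Section {20a} does not mention this task.

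**The concern.** The Friedman, Wilcoxon signed-rank and Sign tests all work on observations linked within a block or pair. Two randomised arms supply no such link. An analyst who followed the text for the primary outcome would have two options, both unsound:

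- **Test each arm separately against its own baseline.** This asks whether patients changed over time. Significance in one arm and not in the other could then be read as a treatment effect.
- **Pair patients across arms.** The result then depends on a pairing that has no basis in the design.

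The fallback is triggered by the observed data and applies to the primary endpoint. The Craving Experience Questionnaire (CEQ) is scored on bounded items, and section {20c} expects about 50 patients, so a failed normality check is plausible. The article gives no distribution for the score, so how likely that is cannot be stated. The trial is open-label, its primary outcome is self-reported, and both arms receive an active exposure therapy. Improvement in both arms is therefore plausible, and that is where within-arm testing misleads most.

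**Working it through.** **Inputs from the article.** 54 patients randomised 1:1 give 54 / 2 = 27 per arm. Sample size {14} states "given a 0.05 statistical significance threshold, a 0.95 statistical power, and accounting for potential dropouts in our hospitalized inpatients" and a large effect, with no numerical d and no dropout rate. An independent t-test at two-sided 0.05 with d = 1.0 needs 27 per arm (power 0.950), so 54 is reproduced at d = 1.0 with no allowance for dropout. At d = 0.8 the same calculation gives 84. This point does not depend on which was meant; 54 is used here only to set 27 per arm.

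**Assumptions (not in the article).** Change scores have SD 1. This is what a baseline-to-follow-up correlation r of 0.5 implies: SD of change = SD × √(2(1 − r)) = SD × √(2 × 0.5) = SD. Distributions are normal except where stated.

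**Test against design**

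| Named test | Data it needs | Supplied by the two arms? |
|---|---|---|
| Friedman (effect size Kendall's W) | Repeated measures within blocks | No |
| Wilcoxon signed-rank | Pairs, or one sample of differences | No |
| Sign | Pairs, or one sample of differences | No |

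**Used within each arm, with no true arm difference**

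- Both arms improve by 0.8 SD: signed-rank at 0.025 (Bonferroni for two arms) rejects in about 95% of trials in each arm.
- Both arms improve by 1 SD (Laplace data, level 0.05): signed-rank rejects in 99.9% and 99.8% of trials in the two arms, and the Sign test in 99%. The rank-sum test between the arms rejects in 4.6%.
- Both arms improve by 0.5 SD: if each arm rejects with probability p, exactly one arm is significant with probability 2p(1 − p). At level 0.025, p is about 0.58, giving 2 × 0.58 × 0.42 = 0.49. At level 0.05 the simulated figure is 44% (5,000 trials). The rank-sum test between the arms rejects in 5.3%.

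**Used across arms with arbitrary pairing.** One simulated data set (t-test p = 0.031, rank-sum p = 0.012) was re-paired at random 5,000 times:

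| Test | Lowest p | Central 95% of pairings | Highest p |
|---|---|---|---|
| Signed-rank | 0.0008 | 0.006 to 0.081 | 0.135 |
| Sign | 0.0003 | 0.0015 to 0.44 | 1.0 |

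The signed-rank result was below 0.05 in 81% of pairings and above it in the rest, with the data unchanged. With unequal arms (27 and 26) the paired test cannot be run at all.

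**Power at d = 0.8, 27 per arm (6,000 trials).** t-test 0.82; rank-sum 0.80; arbitrarily paired signed-rank 0.79; Sign 0.47. The Sign step gives up 0.80 − 0.47 = 0.33, or 33 percentage points. The simulated t-test value agrees with the exact noncentral-t power of 0.822.

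**The case against.** The strongest reply is that the paragraph covers primary and secondary outcomes together and has compressed two analyses into one. Friedman followed by Bonferroni-corrected signed-rank contrasts is the usual sequence for three related measurements, and the task at inclusion has exactly three exposures per patient. Two arms leave nothing for Bonferroni contrasts to separate. Cliff's delta, which suits independent groups, stands in the same sentence as Kendall's W. On this reading the paired tests are right for the task they were meant for, and the arm comparison simply has no fallback stated in the article.

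That reading is plausible, but the text does not state it. The fallback follows directly after the primary arm comparison, the Sample size section itself calls PCET a condition, and Kendall's W is attached to changes across treatment arms. Cliff's delta is an effect size and does not supply a test. Even if the reading is right, the paragraph must say which tests belong to which comparison.

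Four narrower points stand:

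- The high within-arm rejection rates are power to detect real change over time. They become misleading only if read as evidence about the arms, and the article does not announce such an inference.
- With random pairing, the signed-rank test keeps its type I error on average (5.0%) and loses almost no power. Its fault is that the result depends on the pairing chosen.
- The p-value extremes come from one simulated data set.
- Paired tests are also legitimate for changes within a patient across visits, not only for the task at inclusion.

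**Conclusion.** The concern holds. The article specifies tests that do not fit the comparison they follow, and this is an error in stated text, not a detail left to an analysis plan. The primary independent t-test is itself suited to the design, so the damage arises only if the non-normality rule is triggered. In that case the plan would answer a question about time, or give a result that depends on an arbitrary pairing, or, with the Sign test across arms, have about 47% power where 80% is available at d = 0.8. When both arms improve equally by 0.5 SD, a split verdict (one arm significant, the other not) arises in roughly 44% to 49% of trials, depending on the level used. These sizes rest on 27 per arm and change scores with SD 1. The mismatch between tests and design rests on no assumption. It must be corrected because it concerns the primary endpoint of a superiority trial.

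**What to change.** In section {20a}:

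1. For all comparisons between arms, name the Wilcoxon rank-sum (Mann-Whitney) test on the change score as the alternative to the t-test. Van Elteren's test stratified by centre is a good choice, since randomisation is stratified by centre. Report the Hodges-Lehmann shift with its 95% CI and the Cliff's delta already listed.
2. State that Friedman, signed-rank and Sign tests, with Kendall's W, apply only to within-patient comparisons, such as the neutral, VR and picture exposures at inclusion. Remove Kendall's W from the effect sizes for the arms.
3. Drop the symmetry-based switch to the Sign test for arm comparisons.

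A permutation or bootstrap interval for the mean difference between arms would also serve, but is optional.

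The cost is a few sentences, with no change to data collection or patient burden. In the simulations above, the rank-sum test held its type I error at 4.6% to 5.3%. If it became the primary test and d = 1.0 is assumed, 95% power would need about 27 / 0.955 = 28.3, so 29 per arm. In the worst case it would need 27 / 0.864 = 31.3, so 32 per arm. The planned number is 27 per arm.
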